### Control Group

2.5

Participants assigned to the control group will receive a beverage that visually resembles the beetroot supplement. The placebo drink will consist of a neutral solution containing 0.4 mg/mL citric acid, 0.2 mg/mL food coloring, and 0.25 g/mL sugar, formulated to match the appearance, taste, and texture of the beetroot juice without containing nitrates, vitamin C, or polyphenols.

The beetroot juice intervention will be similarly supplemented with 0.25 g/mL sugar to ensure identical sweetness and caloric content, maintaining effective blinding. Both drinks (240 mL each) will be prepared by a third‐party supplier to ensure consistency and double‐blinding.

After a 3‐h interval, a baseline blood sample will be collected from the subjects. The Wingate upper body functional test will be performed immediately thereafter, followed by the Wingate lower body test, which will be conducted 1 to 4 min later. Blood samples will be collected immediately after the Wingate lower body test and again 24 h later. Additionally, participants will complete the RPE questionnaire during both test sessions.

Given that the half‐life of nitrate is approximately 5 to 8 h, a 14‐day washout period is considered sufficient to effectively reduce any residual effects that may arise from prior nitrate supplementation [35]. Since participants will serve as their own controls, sessions will be scheduled at the same time each day to maintain consistency.

The study's design is illustrated in Figure 3. Throughout the experimental phase, each participant will complete two visits to the laboratory.

Studies have also demonstrated that the performance of high‐intensity lower body exercises is not significantly compromised by prior upper body activity. As such, it will be feasible to conduct lower body testing and training either preceding or following upper body sessions without negatively affecting the power output of the lower body [36]. In this study, we will administer the upper body Wingate test, followed by the lower body Wingate test. This sequential testing design will enable a thorough assessment of the effects of the two supplements on performance across different muscle groups.

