### Protocol Version and Trial Status

2.1

This protocol is version 1.0, dated 1 August 2025. Recruitment has not yet commenced and is planned to begin in September 2025, with completion expected by December 2025.

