### Study Design and Setting

2.2

This double‐blind, crossover study will involve 28 semi‐professional wrestlers, who will receive both vitamin C‐enriched beetroot juice and placebo in random order, separated by a 14‐day washout period. Participants will be selected by their respective wrestling coaches and will be randomly assigned to receive either a 240 mL dose of a vitamin C‐enriched beetroot juice or a placebo. The beetroot juice will contain 8.4 mmol of nitrate derived from beetroot powder produced through a freeze‐drying process, along with natural mineral nitrate (3.2%), phenolic compounds, ascorbic acid, carotenoids, and betalains. Additionally, the beetroot juice for the intervention group will include 90 mg of vitamin C, with no additives or preservatives. The 90 mg dose of vitamin C was chosen based on pharmacokinetic data showing that intakes in the 75–100 mg range achieve near‐maximal plasma saturation in healthy adults [32], thereby supporting nitrate‐related nitric oxide processes without entering high‐dose pharmacological ranges that could potentially interfere with adaptive signaling.

The following inclusion criteria will be adopted:
Healthy semi‐professional wrestlers aged 18–24 years.Interested in participating in the project and following the study protocol.Having more than 2 years of wrestling experience.Not being an elite athlete.Not performing any type of physical exercise 72 h before each session.The exclusion criteria will be as follows:Smoking or consuming alcohol.Consuming caffeine‐containing drinks 24 h before the start of the intervention.Having a history of cardiovascular, lung, metabolic, neurologic, or orthopedic disorders that could limit cycle ergometry performance.Utilizing nitrate‐containing pharmaceuticals, such as nitroglycerin or isosorbide.Taking nutritional supplements in the 6 months prior to the study onset.Using mouthwash or oral antiseptic within the past 4 weeks.Taking any herbal medicine.Having an allergy to red beets.

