### Intervention Group

2.4

Participants in the intervention group will be administered a single sports drink containing a blend of red beets and vitamin C (8.4 mmol of nitrate and 90 mg of vitamin C). After a 3‐h interval, baseline blood samples will be collected from the subjects. The Wingate upper body functional test will be conducted immediately thereafter, followed by the Wingate lower body test, which will occur 1 to 4 min later. Blood samples will be obtained immediately following the Wingate lower body test and again 24 h later. Additionally, participants will complete the RPE questionnaire during both testing sessions.

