### Secondary Outcomes

2.7

Secondary outcome measures will include anaerobic mean power, anaerobic minimum power, time to peak power, fatigue index, and various indicators to evaluate muscle damage, including levels of creatine kinase, lactate dehydrogenase, and blood glucose.

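### Adding the same sugar to both drinks does not make them equal in calories, because only the active drink also contains beetroot powder

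*Protocol article*

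**What the plan says.** The Control Group section (2.5) describes the placebo as a neutral solution with "0.4 mg/mL citric acid, 0.2 mg/mL food coloring, and 0.25 g/mL sugar", designed to resemble the beetroot juice in look, taste and texture but free of nitrate, vitamin C and polyphenols. Of the active drink it says: "The beetroot juice intervention will be similarly supplemented with 0.25 g/mL sugar to ensure identical sweetness and caloric content, maintaining effective blinding". The words at issue are "to ensure identical sweetness and caloric content". Each drink is 240 mL, and a third-party supplier makes both.

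The active drink is described in two other places. The Intervention Group section (2.4) calls it "a single sports drink containing a blend of red beets and vitamin C". Study Design and Setting (2.2) says it holds "8.4 mmol of nitrate derived from beetroot powder", along with "natural mineral nitrate (3.2%), phenolic compounds, ascorbic acid, carotenoids, and betalains". No energy or sugar content is given for the powder.

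Secondary Outcomes (2.7) includes "levels of creatine kinase, lactate dehydrogenase, and blood glucose". In the Participant Timeline (2.3) the drink is given at 0 h and the first blood sample is drawn at 3 h.

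**The concern.** Equal sugar added to two unequal bases leaves the bases unequal. The placebo base is described as a neutral solution, while the active base contains beetroot powder. The recipe as written therefore does not produce the calorie match that the section claims for it.

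Two things depend on that match. First, the section presents it as the means of keeping the blind. Second, blood glucose is a listed outcome, and any difference in carbohydrate travels with the treatment in both periods. The crossover does not remove such a difference, because every within-participant contrast contains it. Baseline adjustment cannot remove it either, because the sample called baseline is taken after the drink and the stated schedule has no pre-drink glucose value. A reader who accepts the claim would attribute a glucose difference to nitrate, vitamin C or polyphenols when part of it could come from sugar.

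**Working it through.** **Inputs from the article.** Volume 240 mL; sugar 0.25 g/mL in each drink; citric acid 0.4 mg/mL and coloring 0.2 mg/mL in the placebo (2.5); nitrate 8.4 mmol from powder, and the figure 3.2% (2.2).

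**Assumptions not in the article.** Sugar supplies 4 kcal/g. The neutral base has no energy beyond its listed ingredients. The 3.2% is the nitrate mass fraction of the powder; the text does not say so, and three readings are shown.

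**Plan's implied figure.** Identical caloric content means a difference of 0 kcal.

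**Step 1, sugar.** 0.25 g/mL × 240 mL = 60 g; 60 g × 4 kcal/g = 240 kcal in each drink. The added sugar is equal.

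**Step 2, other placebo ingredients.** (0.4 + 0.2) mg/mL × 240 mL = 144 mg. Even at 4 kcal/g throughout, 0.144 g × 4 = 0.576 kcal. The 90 mg of vitamin C in the active drink is similarly trivial and is ignored.

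**Step 3, powder mass in the active drink.** Mass = 0.0084 mol × molar mass ÷ 0.032.

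| Reading of 3.2% | Nitrate (g) | Powder (g) |
|---|---|---|
| Nitrate ion (62.005 g/mol) | 0.521 | 16.28 |
| Sodium nitrate (84.99 g/mol) | 0.714 | 22.31 |
| Potassium nitrate (101.1 g/mol) | 0.849 | 26.54 |

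**Step 4, energy difference, added-sugar reading.** With powder mass m and energy density e,

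active − placebo = (240 + m·e) − (240 + 0.576) = m·e − 0.576 kcal.

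This is zero only if e = 0.576/m: 0.035 kcal/g (0.576/16.28), 0.026 kcal/g (0.576/22.31) or 0.022 kcal/g (0.576/26.54). The powder would have to be almost free of energy. The stated 0 kcal is not reproduced, and the sign is positive for any ordinary food powder.

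**Step 5, final-concentration reading.** If 0.25 g/mL is the total sugar in the finished active drink and s is the sugar in the powder, 60 − s grams are added. Then

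active − placebo = m·e − 4s − 0.576 kcal.

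Total sugar matches at 60 g. What remains is the powder's non-sugar energy, less 0.576 kcal.

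**Scale, illustration only.** If e were 2 to 4 kcal/g (assumed), the powder would supply 33 to 65 kcal on the ion reading (16.28 × 2; 16.28 × 4), and up to 106 kcal on the potassium salt reading (26.54 × 4). Nothing in the article supports a particular value.

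**The case against.** The strongest reply has three parts.

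**The wording allows another reading.** Since the stated purpose is matching, the sentence may mean that the active drink is brought to the placebo's 0.25 g/mL. Total sugar then agrees, and the sugar-based concerns about glucose and sweetness largely disappear. This reading is possible, but to supplement a juice with a quantity of sugar ordinarily means to add that quantity. A supplier following the sentence literally would add 60 g.

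**The recipe may not be complete.** The composition of the neutral base is not given, the article is condensed, and a supplier prepares the drinks. An offset in the base cannot be excluded, so the break-even figures in Step 4 hold only for an energy-free base and a complete ingredient list. This limits the precision of the check. It does not rescue the sentence, because the mechanism the article names is the equal sugar, and that mechanism alone does not give the result claimed.

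**The consequences are thin.** This largely stands. Both drinks supply about 240 kcal from sugar 3 h before testing, and a modest calorie gap is not something a participant can directly perceive.

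A reader might infer that the blind is compromised or that peak power is biased. The article supports neither: it does not show that participants could taste a difference, and nothing in it links a gap of unknown size to the Wingate results. A reader might also infer that the calorie claim fails on either reading of 0.25 g/mL. On the final-concentration reading, that depends on the powder's non-sugar energy and on the base, neither of which is documented.

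**Conclusion.** On the plain added-sugar reading, the recipe in the Control Group section does not deliver identical caloric content. The active drink has more energy than the placebo, and more sugar if the powder contains any; identical sweetness is therefore not assured. The direction rests on the powder having energy above a few hundredths of a kcal per gram and on the placebo having no undisclosed offset. The size cannot be derived from the article, and no kcal figure should be cited as the gap.

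The weight is modest. The point concerns the interpretation of blood glucose, for which there is no pre-drink sample, and a stated support for blinding that the recipe does not establish. Sample size and error rates are unaffected, and no effect on peak power is shown. It is worth correcting because the remedy is cheap before the drinks are made.

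**What to change.** In the Control Group section:

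- Define 0.25 g/mL as the total sugar concentration of each finished drink (60 g in 240 mL).
- Obtain the powder's sugar and energy content from the supplier. If the powder dose contains s grams of sugar, add 60 − s grams to the active drink.
- Replace the claim of identical sweetness and calories with a claim of equal total sugar. Let the blinding statement rest on the matching of appearance, taste and texture that the section already sets as its aim.
- Report any remaining energy difference between the finished drinks and list it under Limitations (3.1).

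A non-sweet energy source in the placebo could close the remaining gap, but it might disturb the taste and texture match. It is optional and not part of this recommendation.

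The cost is small: composition data from the supplier, one adjusted ingredient, and a few changed sentences. Visits, design and sample size stay as they are. The Protocol Version and Trial Status section (2.1) says "Recruitment has not yet commenced", with a planned start in September 2025, so the change has to be made before then. If the drinks have already been made, the wording correction and the limitation can still be added.

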### Primary Outcomes

2.6

The principal outcome measure for this study will be the anaerobic maximum power attained during the two‐stage Wingate test.

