### Objectives

1.1

The primary objective is to evaluate the acute effects of vitamin C‐enriched beetroot supplementation on maximal anaerobic power during upper and lower body Wingate tests in semi‐professional wrestlers.

Secondary objectives include assessing impacts on mean anaerobic power, fatigue index, time to peak power, and muscle damage markers (creatine kinase, lactate dehydrogenase, blood glucose), as well as ratings of perceived exertion.

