### Device Base Parameters

2.19

To evaluate upper body Wingate test indices, a Monark cycle ergometer (Ergomedic 891E, Vansbro, Sweden) will be used, and to evaluate lower body Wingate test indices, a Monark cycle ergometer (Ergomedic 891E, Vansbro, Sweden) will be utilized. The load (kgf) will be set at 7.5% of each participant's body weight for the lower body Wingate test and 5% of body weight for the upper body Wingate test [40].

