### Statistical Analysis

2.21

Data will be analyzed using SPSS v26. Normality will be assessed via the Shapiro‐Wilk test. Comparison of the within‐subject effects of BRJ (90 mg vitamin C) versus placebo will be evaluated using paired t‐tests (for normal data) or Wilcoxon signed‐rank tests (for non‐normal data). A univariate General Linear Model (GLM) will be used to assess treatment, sequence, and treatment‐sequence (carryover) effects. Statistical significance will be set at *p* < 0.05.

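### The primary endpoint is not uniquely defined: one maximum power is named, but each visit yields an upper-body and a lower-body peak power, with one unadjusted 5% threshold

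*Protocol article*

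**What the plan says.** Section 2.6 (Primary Outcomes) presents the endpoint in the singular: "The principal outcome measure for this study will be the anaerobic maximum power attained during the two‐stage Wingate test". It does not say how one value is obtained from two stages.

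Other sections describe two tests:

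- Section 1.1 (Objectives) sets the primary objective as the effect on "maximal anaerobic power during upper and lower body Wingate tests in semi‐professional wrestlers".
- Section 2.5 (Control Group) fixes the order: "In this study, we will administer the upper body Wingate test, followed by the lower body Wingate test". Sections 2.3 to 2.5 put the second test 1 to 4 minutes after the first.
- Section 2.5 also gives the reason for the sequence, a "thorough assessment of the effects of the two supplements on performance across different muscle groups".
- Section 2.19 (Device Base Parameters) sets different loads: 7.5% of "body weight for the lower body Wingate test and 5% of body weight for the upper body Wingate test".

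Section 2.21 (Statistical Analysis) plans paired t-tests or Wilcoxon signed-rank tests, plus a general linear model for treatment, sequence and carryover. It gives one threshold: "Statistical significance will be set at" p < 0.05. It mentions no combined score, ordering of the two tests, or division of alpha. Section 2.8 sizes the trial for one comparison at two-sided 5% and 80% power.

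**The concern.** A primary endpoint should be one that two analysts, given the same data, would compute in the same way. Here they might not. Section 2.6 can be read in at least three ways:

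1. two endpoints, one per limb;
2. the larger of the two peaks at each visit;
3. some combination, such as a sum or mean.

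These answer different questions and can give different results, most plainly if the supplement affects one limb and not the other.

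Under the first reading there are two primary comparisons and one unadjusted threshold. If significance on either limb were then taken as a positive trial, the chance of a false positive finding on the primary question would exceed the nominal 5%. The protocol text would give a reader no basis for objecting to that choice.

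**Working it through.** **1. The plan's own figure.** Section 2.8 gives SDs of 117.55 W and 112.28 W, means of 508.14 W and 607.36 W, k = 1, two-sided 5% (1.96) and 80% power (0.8416).

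- Difference: 607.36 − 508.14 = 99.22 W; squared, 9844.61.
- Sum of variances: 13818.00 + 12606.80 = 26424.80.
- n = 26424.80 × (1.96 + 0.8416)² / 9844.61 = 26424.80 × 7.849 / 9844.61 = 21.07, rounded up to **22**.

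The stated 22 reproduces. It is the number for a single comparison at 0.05.

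**2. Error rate if both limbs are tested at 0.05 and either counts.** With independent test statistics, the chance of at least one false rejection is 1 − 0.95² = 0.0975.

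The same wrestlers do both tests minutes apart, so positive correlation r between the two test statistics is likely. The article gives no value, so r is an assumption. From the bivariate normal distribution, 1 − P(|Z₁| < 1.96 and |Z₂| < 1.96) is:

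| Assumed r | Two-sided family-wise error |
|---|---|
| 0 | 9.75% |
| 0.3 | 9.5% |
| 0.5 | 9.1% |
| 0.7 | 8.3% |
| 0.8 | 7.8% |
| 0.9 | 7.0% |

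Simulated paired t-tests with 22 and 28 participants (100,000 runs each) agree: 9.7% at r = 0, 9.0% at 0.5, and 7.1% to 7.2% at 0.9.

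**3. False claims of benefit only.** If only results favouring beetroot count, the either-limb error is about 4.9% at r = 0 and 3.9% at r = 0.8, against 2.5% for one test.

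**4. Readings with no inflation.** If both limbs must be significant, the error is at most 5%. If one combined value is tested once, it is 5%.

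**5. Cost of controlling the error.** At 0.025 the normal quantile is 2.2414, and the formula in step 1 gives n = 26424.80 × (2.2414 + 0.8416)² / 9844.61 = 26424.80 × 9.505 / 9844.61 = 25.51, rounded up to **26**.

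In detectable difference, for a paired t-test with 22 completers and 80% power, the SD of the within-person difference is √(26424.80 − 2ρ × 117.55 × 112.28). The article gives no within-person correlation ρ, so a range is shown:

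| Assumed ρ | SD of difference | Detectable at 0.05 | Detectable at 0.025 |
|---|---|---|---|
| 0 | 162.6 W | 102 W | 114 W |
| 0.9 | 51.6 W | 32 W | 36 W |

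Section 2.8 describes its SDs as mean-power data, while the primary outcome is maximum power. The sample sizes and watt figures are therefore only indicative for peak power.

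**The case against.** The strongest reply is that multiplicity rules and success criteria are commonly left to a statistical analysis plan. One may exist here, and a journal article condenses the full protocol. That holds for the mechanics of adjustment, and the absence of an alpha rule alone would not be a finding. It does not answer the main point. The article itself names the primary endpoint, and does so in terms that its own objective and procedures do not resolve.

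A reader might also infer that the plan commits to testing each limb at 0.05, that success on either would be reported as a positive trial, and that the error rate is therefore nearly 10%. The text does not support this. Section 2.21 gives one threshold and never says it applies to each limb, and no section states an either-limb rule. The 9.75% also requires independent test statistics, which is unlikely in the same men minutes apart, and it counts false findings in both directions although section 1.2 hypothesises benefit. Nor can it be said that the limb would be chosen after seeing the data, because the analysis plan is not available.

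It is also tempting to say that the larger of the two peaks would almost always come from the lower body. The heavier lower-body load makes this plausible, but the article gives no power data by limb, and the point does not depend on it.

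**Conclusion.** The point stands as a defect in how the primary endpoint is defined. Section 2.6 names one value, section 1.1 and the procedures produce two, and nothing in the article links them.

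The consequence for the error rate is conditional. It requires that both limbs are tested at 0.05 and that either may carry the trial. On those assumptions the two-sided family-wise error is about 7.0% to 9.75%, depending on a correlation that the article does not give. Under a both-limbs rule or a single combined value the inflation disappears, so the figure measures what the wording permits and not what the trial will necessarily do.

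This should be corrected: the ambiguity concerns the primary endpoint, the possible inflation is moderate, and the remedy is small.

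**What to change.** In section 2.6, name two primary endpoints: peak power on the upper-body test and peak power on the lower-body test. In section 2.21, state that they are tested by Holm at an overall two-sided 5%, and that the trial is positive if at least one is significant after adjustment.

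Naming one limb as the single primary endpoint and the other as secondary would cure the problem equally and would need no alpha adjustment. A defined combined value or a rule that both must be significant would also remove the ambiguity. What matters is that one is chosen and written down before the data are seen.

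The text change is about one sentence in each section. The version shown (section 2.1) says recruitment had not begun, and section 2.24 gives the amendment route. The statistical cost of Holm is that the smaller p-value must fall below 0.025. By the article's formula this needs 26 completers instead of 22. With 28 planned, the dropout allowance shrinks from 6 of 28 (21.4%) to 2 of 28 (7.1%).

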### Secondary Outcomes

2.7

Secondary outcome measures will include anaerobic mean power, anaerobic minimum power, time to peak power, fatigue index, and various indicators to evaluate muscle damage, including levels of creatine kinase, lactate dehydrogenase, and blood glucose.

### Power Calculation and Sample Size Estimate

2.8

Sample size was calculated based on mean power data from a previous study by Williams et al. (2020) [37] (placebo: 508.14 ± 117.55 W; BRJ: 607.36 ± 112.28 W). The required sample size was calculated to be 22 participants for a crossover design considering 95% confidence and 80% power using the following equation:

$$n=\frac{(k\times \delta_{1}^{2}+\delta_{2}^{2}){\left(Z_{1-\alpha /2}+Z_{1-\beta }\right)}^{2}}{{∆}^{2}}.$$

In the above equation, n is the sample size in each group, k is the ratio of the groups (which is 1 in this study), δ is the standard deviation in each group, Δ is the difference of group means, Z_{1‐α/2} is considered 1.96 for a 95% confidence interval, and Z_{1‐β} is the power of the study. To account for potential participant dropout and ensure completion of all study sessions, 28 participants were recruited.

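### The 22 participants and 80% power are justified on mean power, a secondary outcome, with an independent-groups formula; power for the primary outcome, maximum power, is undocumented

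*Protocol article*

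**What the plan says.** Section 2.6 of the protocol article fixes the primary outcome: "The principal outcome measure for this study will be the anaerobic maximum power attained during the two‐stage Wingate test". The abstract and Section 1.1 agree that it is maximum power. Section 2.7 places mean power lower: "Secondary outcome measures will include anaerobic mean power".

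Section 2.8 then sizes the trial: "Sample size was calculated based on mean power data from a previous study". The inputs are "placebo: 508.14 ± 117.55 W; BRJ: 607.36 ± 112.28 W". The result is given as "22 participants for a crossover design considering 95% confidence and 80% power". The formula adds the two group variances, and its terms are defined as "n is the sample size in each group, k is the ratio of the groups (which is 1 in this study". The number is raised to 28 to allow for dropout.

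Section 2.21 plans paired t-tests, or Wilcoxon signed-rank tests for non-normal data, for the treatment comparison, and Section 2.20-level detail elsewhere in the article adds nothing on power. Section 2.5 notes that each participant acts as his own control. Nowhere does the article give a difference or SD for maximum power, an SD of within-participant differences, or a within-participant correlation.

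**The concern.** Two things in Section 2.8 do not fit the rest of the plan.

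First, the outcome. The calculation is for mean power, and the article does not argue that mean power stands in for maximum power. The two are different quantities from the same test and need not share an SD or a treatment effect. A reader who meets a single power statement in a protocol will normally take it to cover the primary outcome, and here it does not.

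Second, the design. The formula returns a number per group for a comparison of two separate sets of people. Section 2.8 reports that number as the total for a design in which the same people supply both measurements. The variance of a paired difference depends on the correlation between visits, and that term is missing.

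At stake is the only numerical justification for the size of the trial. The limitations section (3.1) mentions the modest sample only in relation to secondary biochemical markers, so nothing there tells the reader that the primary outcome has not been powered on its own figures.

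**Working it through.** **Inputs (Section 2.8).** SD on placebo 117.55 W; SD on beetroot juice 112.28 W; difference 607.36 − 508.14 = 99.22 W, which is 99.22 / 508.14 = 19.5% of the placebo mean; two-sided alpha 0.05 (z = 1.96); power 80% (z = 0.8416); k = 1. All refer to mean power. The within-participant correlation (rho) is not given, so a range of 0 to 0.9 is assumed below.

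**Step 1: reproduce the stated figure.**

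n = (117.55² + 112.28²)(1.96 + 0.8416)² / 99.22² = 26,424.8 × 7.849 / 9,844.6 = 21.07, rounded up to 22.

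The arithmetic is correct. As the formula is defined, this is 22 per group, or 44 people in a parallel-group trial.

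**Step 2: the same inputs in a paired design.** The variance of the within-participant difference is

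SD_diff² = SD1² + SD2² − 2 × rho × SD1 × SD2.

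At rho = 0 this is 26,424.8, so SD_diff = 162.6 W, and the paired normal-approximation formula n = SD_diff²(1.96 + 0.8416)² / 99.22² is identical to Step 1. At rho = 0.5 it is 26,424.8 − 13,198.5 = 13,226.3, so SD_diff = 115.0 W.

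Power, required n and detectable difference were then taken from the noncentral t distribution for a paired t-test. Power is for 99.22 W; the detectable difference is at 80% power.

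| rho (assumed) | SD_diff, W | n, normal approx. | n, paired t | Power, 22 completers | Power, 28 completers | Detectable, n = 22, W | Detectable, n = 28, W |
|---|---|---|---|---|---|---|---|
| 0 | 162.6 | 22 | 24 | 77.9% | 88% | 101.8 | 89.3 |
| 0.3 | 136.0 | 15 | 17 | 90.3% | 96% | 85.2 | 74.7 |
| 0.5 | 115.0 | 11 | 13 | 97.1% | 99% | 72.0 | 63.2 |
| 0.7 | 89.1 | 7 | 9 | over 99% | over 99% | 55.8 | 49.0 |
| 0.8 | 72.9 | 5 | 7 | over 99% | over 99% | 45.6 | 40.0 |
| 0.9 | 51.6 | 3 | 5 | over 99% | over 99% | 32.4 | 28.4 |

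So 22 in total agrees with the paired normal approximation only at rho = 0. Even there the t-test falls about 2 points short of 80% with 22 completers. At any of the positive values shown, power for 99.22 W is well above 80%.

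**Step 3: the primary outcome.** The same calculation for maximum power needs a difference and an SD of differences (or two SDs and rho) for upper- and lower-body maximum power. None is in the article, so no power figure can be computed. Every row of the table is for mean power and cannot be carried over.

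**The case against.** The case for leaving the paragraph alone has real force on four points.

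- The arithmetic is right: 21.07 does round up to 22.
- Leaving out a positive correlation errs on the safe side. On the stated inputs the only shortfall is about 2 percentage points, at zero correlation with exactly 22 completers; with all 28 completing, power is about 88% even there. This stands. The formula point is one of wording and method, and it does not threaten the trial.
- Section 2.8 names mean power openly and does not expressly attach the 80% to the primary outcome. This also stands, but a protocol's only power statement will be read that way unless the text says otherwise.
- After a null result, the confidence interval for the paired difference shows which effects are excluded. The planning calculation does not do that job, so an imperfect one does not deprive the reader of the answer.

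A reader might go further and infer that the trial is underpowered for maximum power, or that 44 wrestlers are needed. The documents support neither. Power for maximum power is unknown, not shown to be low, and 44 would apply only to a parallel-group trial.

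What the objection does not answer is the mismatch of outcomes. Nothing elsewhere in the article supplies a maximum-power difference or SD, or a reason to use mean power in its place.

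**Conclusion.** The point holds in two parts of unequal weight.

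The main part is that the sample size is justified on a secondary outcome. Power for the primary outcome is undocumented, and the 80% should not be read as applying to it. This rests only on Sections 2.6 to 2.8 and needs no assumption. It has no numerical size, because the inputs are absent.

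The lesser part is that a per-group result for independent groups is reported as a crossover total. On the mean-power inputs, 80% is not what a paired t-test on 22 completers delivers at any correlation in the assumed range tried: it is 78% at rho = 0, 90% at 0.3 and 97% at 0.5. For non-zero positive correlation the error is conservative for the assumed 99.22 W. These figures assume a paired t-test, normally distributed differences and the SDs quoted in Section 2.8.

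**What to change.** Rewrite Section 2.8 as follows.

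1. Base the justification on maximum power, for the upper- and lower-body tests. Use SD_diff² = SD1² + SD2² − 2 × rho × SD1 × SD2 with a t correction, and state the source of, or the assumption behind, the SDs and rho.
2. Report the detectable difference in upper- and lower-body maximum power with 22 and with 28 completers, over a range of rho that includes low values, for example 0 to 0.9.
3. Say that the 80% refers to mean power only, or drop it.
4. Correct the per-group definition of n so that it matches a crossover total.

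The cost is one paragraph and the work of finding or assuming maximum-power inputs. The planned 28 can stay, with the power statement replaced by these detectable differences. What is given up is any claim of 80% power for the primary outcome. Section 2.1 says recruitment had not begun at this protocol version, so the restatement can be made before data exist.
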